### Statistical Methodology

#### Sample Size Calculation

The G*Power 3.1 (Heinrich-Heine-Universität Düsseldorf) program was used to determine the sample size. The calculation was based on the HADS total score, which is defined as the primary outcome of the study, assuming a repeated-measures design with 3 groups (home-based, face-to-face, and control) and 3 assessment time points (baseline, postintervention, and 4-week follow-up). Considering an α level of .05 and power of .80, an effect size of *f* of 0.25 (moderate) was assumed for the group × time interaction, with an assumed correlation among repeated measures of 0.50 and a nonsphericity correction (ε) of 1.0. Under these assumptions, a sample of at least 42 participants, randomized into the 3 groups, is required. This sample size was calculated to detect differences between groups and was not designed to formally demonstrate equivalence between the interventions. Anticipating a dropout rate of approximately 30% (18/60), a total of 60 participants will be recruited to ensure the necessary final sample size of 42 participants.

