#### Statistical Analysis

The analysis will be conducted using the ITT principle, including all randomized participants. Per-protocol sensitivity analyses will also be performed. For continuous variables, a linear mixed model will be used, with fixed effects for group (face-to-face, home-based, and control), time (baseline, postintervention, and follow-up), and group × time interactions. Participants will be modeled as a random effect. Baseline values will be included as part of the repeated-measures structure rather than as covariates, allowing the estimation of within- and between-group changes over time. Age and sex will be considered as covariates in adjusted models if baseline imbalances or clinically relevant associations with the outcomes are identified. The home-based vs face-to-face comparison will be interpreted based on effect estimates and confidence intervals and will not be treated as a formal equivalence analysis. This model, which treats repeated within-participant measures as a random effect, will be used. An appropriate covariance structure for the repeated measures will be selected based on model fit criteria. This method allows for the management of missing data under the assumption that they are missing at random. In cases of systematic losses, multiple imputations may be used as a complementary analysis.

For categorical or dichotomous variables, the chi-square or Fisher exact tests will be applied, where appropriate. For all hypothesis tests, the α level for statistical significance will be set at *P*<.0, corresponding to a 95% confidence level. To assess the magnitude of significant differences between the preintervention and postintervention moments and between groups, the Hedge *g* (x ®1–x ®2⁄ SD grouped) will be calculated. The effect size magnitudes will be interpreted as follows: <0.2, no effect; 0.2 to 0.4, small; 0.5 to 0.7, moderate; and ≥0.8, large [58]. Secondary outcomes will be analyzed using the same modeling strategy; however, these analyses will be considered exploratory, and no formal adjustment for multiple comparisons is planned. The data will be analyzed using IBM SPSS software, version 20.0, licensed to UDESC, and Microsoft Office Excel for Windows.

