## Discussion

This protocol for a randomized controlled trial (RCT) aims to evaluate the impact of face-to-face and home-based rehabilitation models, compared with a CG without a structured intervention, in the preparation of individuals with severe obesity who are candidates for BMS. Both models combine physical exercise and health education, focusing on improving functional capacity, exercise self-efficacy, quality of life, mental health, and sleep. The primary hypothesis is that the interventions will produce effects superior to those of the control and that the home-based model will exhibit greater adherence by eliminating logistical barriers, such as travel to the intervention site.

It is well established that prehabilitation has been established as a promising approach to optimize functional status and reduce perioperative risks [59,60]. In the context of obesity, studies have reported benefits including reduced BMI, improved physical fitness, enhanced respiratory muscle strength, and positive effects on metabolic parameters [61-65]. However, the literature is currently limited by high methodological heterogeneity regarding exercise type, duration, and intensity, which hinders standardization and limits comparability between studies [66,67].

Previous studies have demonstrated diversity in preoperative interventions for patients undergoing bariatric surgery, while also highlighting essential gaps in care. García-Delgado et al [15] tested respiratory training and measured outcomes related to preoperative weight, while the Bari-Active RCT [35] used a 6-week behavioral intervention with objective monitoring of PA, demonstrating benefits for quality of life. A recent review of home-based prehabilitation [68] indicated that home-based programs can reduce complications and improve functional performance, as well as symptoms of depression and anxiety. However, direct comparisons between home-based and in-person protocols, integrating objective measures of PA and mental health outcomes, are still scarce; this study addresses this gap by standardizing a multimodal intervention using FITT-VP principles, positioning it to resolve current inconsistencies in the evidence.

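### Effect sizes are planned for significant pre-post differences on the same footing as between-group differences, with no statement of which supports a conclusion

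*Protocol article*

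**What the plan says.** All references are to the protocol article.

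- **Statistical Analysis, model.** Continuous outcomes go into a linear mixed model with group, time and group-by-time terms. Baseline is one of the repeated measures, "allowing the estimation of within- and between-group changes over time".
- **Statistical Analysis, effect sizes.** Hedges g is to be calculated for "significant differences between the preintervention and postintervention moments and between groups". One set of labels, from no effect to large, serves both kinds of difference.
- **Statistical Analysis, home-based versus face-to-face.** This comparison is to be read from effect estimates and confidence intervals.
- **Sample Size Calculation.** The trial is sized on the interaction: an *f* of "0.25 (moderate) was assumed for the group × time interaction". The section adds that the aim was to detect differences between groups.
- **Discussion.** "The primary hypothesis is that the interventions will produce effects superior to those of the control".

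The article does not say that pre-post results are descriptive, or that between-group effect sizes will be given when they are not significant.

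**The concern.** For a pre-post difference to count as significant it must first be tested, so the effect-size sentence brings pre-post tests into the plan. It gives their results the same labels as the randomized comparison. Two problems follow.

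1. **A pre-post change is not a randomized comparison.** It takes in anything that moves all arms alike, such as waiting for surgery, repeated questionnaires or being followed up. The stated hypothesis is superiority to control, which a change from baseline does not address. One arm being significant while another is not is no test of the difference between them.
2. **Sizing only significant differences selects the large ones.** With 14 to 20 people per arm, a modest true change reaches significance only when the sample overstates it. The label then describes the overstated value, and arms that miss the threshold get no g.

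At stake is how the results will be read. A report could say that an exercise arm showed a moderate improvement and control none, when the arms changed equally.

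**Working it through.** **Inputs**

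- Alpha and power: "Considering an α level of .05 and power of .80" (Sample Size Calculation). The threshold in Statistical Analysis is misprinted, but "corresponding to a 95% confidence level" points to .05. Two-sided tests are assumed.
- Design: three arms, 1:1:1, and "3 assessment time points (baseline, postintervention, and 4-week follow-up").
- Correlation: "with an assumed correlation among repeated measures of 0.50 and a nonsphericity correction (ε) of 1.0". The SD of change is therefore SD × √(2(1 − 0.50)) = SD, and changes can be given in SDs of the score.
- Arm size: 60/3 = 20 recruited, 42/3 = 14 completing.
- True change common to all arms: not in the document. Assumed range 0 to 1.0 SD.

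**The plan's own figure.** For the interaction, λ = N·m·f²/(1 − ρ) with df (k − 1)(m − 1) and (N − k)(m − 1). With k = 3, m = 3, f = 0.25 and ρ = 0.50, 80% power needs N = 35, or 36 in equal arms (power 0.823). The stated 42 has power 0.887. It is what two time points would give. The difference is on the safe side and does not bear on this point. 42/(1 − 0.30) = 60 agrees with the plan.

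**Step 1: how often the arms would differ in significance.** Let every arm have the same true change d. The chance p that one arm's pre-post test is significant comes from the noncentral t with n − 1 df and noncentrality d√n (paired t test). For independent arms:

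- at least one exercise arm significant, control not: [1 − (1 − p)²](1 − p)
- one named exercise arm significant, control not: p(1 − p)

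| Shared change (SD) | n = 14: p | at least one | named | n = 20: p | at least one | named |
|---|---|---|---|---|---|---|
| 0 | 5.0% | 9.3% | 4.8% | 5.0% | 9.3% | 4.8% |
| 0.2 | 10.7% | 18.1% | 9.5% | 13.6% | 21.9% | 11.8% |
| 0.3 | 18.0% | 26.9% | 14.8% | 24.7% | 32.6% | 18.6% |
| 0.4 | 28.4% | 34.9% | 20.3% | 39.7% | 38.4% | 23.9% |
| 0.5 | 41.0% | 38.5% | 24.2% | 56.4% | 35.3% | 24.6% |
| 0.8 | 79.0% | 20.1% | 16.6% | 92.4% | 7.6% | 7.0% |
| 1.0 | 93.2% | 6.7% | 6.3% | 98.9% | 1.1% | 1.1% |

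Example, n = 20 and 0.4 SD: p = 0.397, so (1 − 0.603²) × 0.603 = 0.384.

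Ceiling: with q = 1 − p, the quantity q − q³ peaks at q = 1/√3, that is p = 0.423, at 2/(3√3) = 0.385. That corresponds to a shared change of 0.51 SD at 14 per arm or 0.42 SD at 20. For one named arm the peak is 0.25 at p = 0.50. At no change, counting improvements only (p = 0.025) gives 4.8% instead of 9.3%.

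**Step 2: what the planned between-arm test does.** In 40,000 simulated trials per setting with no arm difference, the interaction was significant in 4.8-5.1%. The pattern of Step 1 together with a significant interaction occurred in at most about 2.4%.

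**Step 3: inflation from sizing only significant changes.** In a paired t test the observed change must exceed t/√n of its own SD: 2.093/√20 = 0.47 at 20 per arm and 2.160/√14 = 0.58 at 14. By simulation, a true change of 0.3 SD that comes out as a significant improvement averages 0.57 SD at 20 per arm and 0.66 SD at 14. That is 0.57/0.3 = 1.9 and 0.66/0.3 = 2.2 times the truth. Both averages fall in the plan's moderate band (0.5 to 0.7).

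**The case against.** The best defence is that the plan already contains the right analysis. The mixed model has a group-by-time term, the trial is sized on it, and home-based versus face-to-face is to be read from estimates and intervals. The effect-size sentence never says that tests are run separately in each arm; it could mean the overall time effect or contrasts from the model. The article is condensed, and which contrast carries the conclusion is often left to an analysis plan.

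Much of this stands. A reader might infer that the plan commits to separate tests inside each arm and will claim efficacy when an exercise arm is significant and control is not. No section says so. A reader might also infer that the home-based and face-to-face arms would be falsely separated by discordant pre-post P values. The stated basis for that comparison rules this out.

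The 38% also needs care. It is a maximum, reached at a shared change that the document does not give, and it counts either of two exercise arms. Setting it against 5% for one contrast is not like for like: two unadjusted exercise-versus-control tests would err in about 9% of trials.

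What does not stand is the appeal to an unseen analysis plan. The effect-size sentence is printed text. It conditions g on significance and gives pre-post and between-group differences one scale. If it means a pooled time effect, that is no randomized comparison either.

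**Conclusion.** The point holds as a matter of wording and interpretation. The plan sizes and labels significant pre-post differences beside between-group ones without saying which supports a conclusion, and it gives effect sizes only when significant.

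The inflation applies to whatever pre-post g is reported under this rule: roughly a doubling for a true 0.3 SD change at 14 to 20 per arm. The misleading pattern between arms is a risk only if pre-post results are read as intervention effects. Its frequency is then about 9% at no change, 18-22% at 0.2 SD, at most 38% near 0.4-0.5 SD and 1-7% at 1.0 SD. These figures assume an equal true change in all arms, correlation 0.50, two-sided 5% paired tests and independent arms.

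The 38% should not be taken as the trial's false-positive rate. The planned interaction test errs in about 5% of null trials.

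**What to change.** Amend the Statistical Analysis section to say three things:

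1. Conclusions about the interventions rest on between-arm contrasts of change from the mixed model.
2. Those contrasts are reported with effect size and 95% CI whether or not they are significant.
3. Within-arm change is reported descriptively, as an estimate with 95% CI, and is not read as an intervention effect.

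The sentence that ties Hedges g to significance should be replaced accordingly. The cost is wording only: the model, sample size and data collection stay as they are. The downside is fewer P values to report.

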## Results

In August 2025, this clinical trial received funding from the Research Support Program of the UDESC. Participant recruitment and data collection are scheduled to begin in April 2026. Initial assessments and randomization are expected to occur between April and May 2026. The intervention phase is scheduled to be completed in September 2026, followed by data analysis between October and November 2026. Results are expected to be published in mid-2027.

## Discussion

This protocol for a randomized controlled trial (RCT) aims to evaluate the impact of face-to-face and home-based rehabilitation models, compared with a CG without a structured intervention, in the preparation of individuals with severe obesity who are candidates for BMS. Both models combine physical exercise and health education, focusing on improving functional capacity, exercise self-efficacy, quality of life, mental health, and sleep. The primary hypothesis is that the interventions will produce effects superior to those of the control and that the home-based model will exhibit greater adherence by eliminating logistical barriers, such as travel to the intervention site.

It is well established that prehabilitation has been established as a promising approach to optimize functional status and reduce perioperative risks [59,60]. In the context of obesity, studies have reported benefits including reduced BMI, improved physical fitness, enhanced respiratory muscle strength, and positive effects on metabolic parameters [61-65]. However, the literature is currently limited by high methodological heterogeneity regarding exercise type, duration, and intensity, which hinders standardization and limits comparability between studies [66,67].

Previous studies have demonstrated diversity in preoperative interventions for patients undergoing bariatric surgery, while also highlighting essential gaps in care. García-Delgado et al [15] tested respiratory training and measured outcomes related to preoperative weight, while the Bari-Active RCT [35] used a 6-week behavioral intervention with objective monitoring of PA, demonstrating benefits for quality of life. A recent review of home-based prehabilitation [68] indicated that home-based programs can reduce complications and improve functional performance, as well as symptoms of depression and anxiety. However, direct comparisons between home-based and in-person protocols, integrating objective measures of PA and mental health outcomes, are still scarce; this study addresses this gap by standardizing a multimodal intervention using FITT-VP principles, positioning it to resolve current inconsistencies in the evidence.

The face-to-face model enables close monitoring by the multidisciplinary team, fostering the therapeutic bond and facilitating direct observation of the patient’s performance—factors associated with improved clinical outcomes [69,70]. On the other hand, this model presents potential barriers, such as lack of time, travel costs, and access difficulties, especially for individuals in remote areas or with lower socioeconomic status [71].

The home-based model, supported by digital technologies, emerges as a viable alternative, expanding the reach of rehabilitation and maintaining remote professional support through video calls, online platforms, and health apps [72]. Studies show that, when well-structured, home-based programs can achieve functional and clinical outcomes similar to those of face-to-face programs, while also favoring adherence and reducing hospital costs [68,73,74]. In addition, home-based rehabilitation can reduce postoperative complications, length of hospital stay, and psychological symptoms, such as anxiety and depression, while maintaining high levels of participation [68,75-78].

The strengths of this study include rigorous adherence to the SPIRIT guidelines and the detailed description of the intervention protocol using FITT-VP principles, ensuring reproducibility and allowing for direct comparisons between groups. The multimodal intervention, which integrates exercise and health education, can facilitate significant changes in physical, psychological, and behavioral aspects, all of which are fundamental for improving obesity-related outcomes.

Crucially, the study prioritizes high ecological validity and generalizability through a stratified recruitment strategy (targeting 50% participants from low-socioeconomic backgrounds and 20% from rural populations). This approach actively mitigates the selection bias often found in university-based trials and ensures the results reflect diverse, real-world clinical conditions, supporting future broad implementation in public health systems.

The innovation of this study lies in the methodological evaluation of 2 structured prehabilitation formats in the context of BMS, considering physical and psychological outcomes as well as adherence. The inclusion of a CG will allow us to isolate the specific effects of the interventions and provide higher-level evidence to support future guidelines.

However, some limitations must be recognized. Psychological outcomes will be assessed using self-reported instruments, which may introduce reporting bias; the follow-up period will be relatively short, limiting conclusions regarding long-term effects. Regarding the HBG, adherence and exercise execution depend on participant engagement outside a supervised environment. To mitigate this, asynchronous video verification strategies will be used (targeting ≥85% of execution fidelity) to cross-reference self-reported data. In addition, participant blinding will not be feasible due to the nature of the interventions, although outcome assessors and statisticians will remain blinded. This lack of blinding may introduce expectation effects that could influence self-reported psychological outcomes.

Nevertheless, if the hypotheses are confirmed, the results may guide the implementation of prehabilitation programs adapted to the needs and realities of the participants, favoring individual-centered preoperative care and contributing to health policies at lower costs. In addition, they will provide support for the incorporation of evidence-based strategies in face-to-face and home-based modalities, offering safe and affordable options to optimize surgical preparation and improve perioperative outcomes in people with severe obesity awaiting BMS.
